### Allocation to treatment

Care homes will be segmented according to their resident mix (three categories: care home, care home with nursing, care home with residential and nursing beds) and size (i.e. number of beds - again three categories: small, medium and large). Recruitment will then proceed in 'waves'.

In the first wave a relatively homogeneous block of homes with approximately 30 residents will be approached as this represents the optimum number of residents for delivery of the intervention. For the second and subsequent waves, the homes to be approached will be decided purely on the basis of facilitating recruitment. For practical (i.e. workload) reasons, consenting homes will be allocated to intervention or control sequentially after consent is obtained using minimisation. This strategy has the advantage of achieving approximate balance between treatment groups with respect to stratifying factors (here resident mix and size) whilst allowing the practical advantage of being able to make allocations sequentially as homes are recruited, rather than having to wait for blocks to accumulate. Recruitment will cease once approximately 900 residents have been recruited.

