### Sample size estimation

Previous research suggests that medication review services can reduce the average number of falls per patient over a 6 month period by 0.59 (confidence interval: 0.49 to 0.70), with a variance per patient of four [5]. This study was conducted in a similar setting and therefore we estimate the baseline frequency of falls to be similar (approximately 1 per resident per six months). Using the lower end of this confidence interval, 261 patients in each group would be required to detect this difference with 80% power and at the 5% level of significance. Assuming the intra-cluster correlation coefficient is 0.02 then in an average home (30 residents) this sample size needs to be multiplied by 1.58 [29] (the design effect allowing for clustering). Thus a total of 824 patients (412 in each group) will need to be recruited from approximately thirty homes. In recruiting 30 homes with an average of 30 residents this will allow for 10% losses to follow-up.

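### The design effect of 1.58 assumes homes of equal size although the plan enrols small, medium and large homes, so 80% power to detect 0.49 after 10% losses is not assured

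*Protocol article*

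**What the plan says.** All the sizing is in the protocol article, Sample size estimation. The effect comes from an earlier study in which medication review was found to "reduce the average number of falls per patient over a 6 month period by 0.59 (confidence interval: 0.49 to 0.70"). The same study supplies the variance, which is taken as 4 for each resident. "Using the lower end of this confidence interval", that is 0.49, "261 patients in each group would be required to detect this difference with 80% power and at the 5% level of significance". Then, at an intra-cluster correlation (ICC) of 0.02, "in an average home (30 residents) this sample size needs to be multiplied by 1.58". The result is 412 per group, 824 in all, and 30 homes averaging 30 residents are said to cover 10% losses.

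Other sections describe homes that differ in size:

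- Allocation to treatment segments homes by "size (i.e. number of beds - again three categories: small, medium and large") and uses size as a minimisation factor. The first wave is a fairly uniform block of homes near 30 residents, but "For the second and subsequent waves, the homes to be approached will be decided purely on the basis of facilitating recruitment". Recruitment stops at about 900 residents.
- Intervention expects that larger homes will need more than two review meetings.
- Clinical analysis fits home size as a three-level fixed effect.

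No bed cut-offs, size distribution or CV of home size are given.

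**The concern.** For a given mean home size and ICC, the design effect is smallest when all homes are equal. Spread in home size raises it, and quoting the mean alone does not capture this. The sizing therefore uses the most favourable value, while three other sections of the same article expect unequal homes. This is a premise fixed in one section and contradicted in others, not a detail that can be left to an analysis plan.

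What is at stake is the stated justification for 824 residents and 80% power. If power at the planning effect is really a few points lower, an inconclusive falls result would be judged against a somewhat optimistic figure.

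**Working it through.** **Inputs from the article:** difference 0.49; variance 4; two-sided 5% (the article does not state sidedness, but two-sided reproduces its figure); power 80%; ICC 0.02; mean home size m = 30; 15 homes per arm; 10% losses. **Assumed, because not given:** CV of home size.

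**1. The plan's own figures.**
- n per group = 2 x (1.960 + 0.842)^2 x 4 / 0.49^2 = 261.5 (plan: 261).
- Design effect = 1 + (30 - 1) x 0.02 = 1.58.
- 261 x 1.58 = 412.4 per group, about 824 in total.
- Power = Phi(0.49 / sqrt(8 x DE / n per group) - 1.96); with DE = 1.58 and n = 412 this is 79.9%.

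Everything reproduces.

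**2. The loss allowance with equal homes.** 900 x 0.9 = 810, or 405 per group and 27 per home. DE = 1 + 26 x 0.02 = 1.52, and power is 80.7%. So 810 suffices although it is below 824, because smaller homes carry a smaller design effect. The reserve is 0.7 points.

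**3. Unequal homes.** Two design effects bracket the analysis:
- (a) residents weighted equally: DE = 1 + ((1 + CV^2) x m - 1) x 0.02;
- (b) efficiently weighted mixed model: DE = [1 + (m - 1) x 0.02] / [1 - CV^2 x L(1 - L)], with L = 0.02m / (0.02m + 0.98). At m = 27, L = 0.54/1.52 = 0.355 and L(1 - L) = 0.229.

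Example for (a), CV 0.5, 810 analysed: DE = 1 + (1.25 x 27 - 1) x 0.02 = 1.655; standard error = sqrt(8 x 1.655 / 405) = 0.181; power = Phi(0.49/0.181 - 1.96) = 77.3%.

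| Assumed CV | DE at m = 30, (a) | Total required, 2 x 261.5 x DE | Power at 810, (a) | Power at 810, (b) | Power at 900, (a) | Power at 900, (b) |
|---|---|---|---|---|---|---|
| 0 | 1.58 | 826 | 80.7% | 80.7% | 83.2% | 83.2% |
| 0.4 | 1.68 | 877 | 78.5% | 79.3% | 81.0% | 81.8% |
| 0.5 | 1.73 | 905 | 77.3% | 78.4% | 79.8% | 81.0% |
| 0.6 | 1.80 | 939 | 75.9% | 77.3% | 78.3% | 79.9% |

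The 826 at CV 0 is the plan's 824 without rounding 261.5 down.

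**4. Where 80% is lost.** With 405 per group the largest tolerable design effect is 405 / 261.5 = 1.549. At m = 27 this is reached at CV 0.23 under (a) and 0.28 under (b). With all 900 contributing in full, the thresholds are about 0.48 and 0.59.

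**5. Scale.** Equal thirds of homes with 20, 30 and 40 residents have CV 0.27; with 15, 30 and 45, CV 0.41. These are illustrations, not figures from the article.

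**6. Detectable difference.** At CV 0.5 with 810 analysed, (a) gives 2.802 x 0.181 = 0.51 at 80% power, against 0.49.

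**The case against.** Several points on the other side stand.

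- **The shortfall is conditional.** A reader might infer that the trial does not deliver 80% power. The article does not support that: it gives no spread of home sizes, the uniform first wave pulls the CV down, and below about 0.23 the target is met even with 810 analysed. Nor is there an arithmetic slip, since every stated figure reproduces.
- **The analysis may recover part of the loss.** Formula (a) suits an analysis that weights residents equally. Efficient weighting costs less, as columns (b) show.
- **810 is a pessimistic count for falls.** Clinical analysis aggregates events with resident days at risk, so a resident who dies or leaves still contributes until then. The 810 and 900 columns are the two ends.
- **The planning effect is cautious.** The plan sizes on the lower confidence limit. At 0.59, power with 810 analysed and CV 0.6 is still Phi(0.59 / sqrt(8 x 1.714 / 405) - 1.96) = 89%. However, the plan claims its 80% for 0.49.

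A second tempting inference is that, because falls are analysed at home level, small and large homes count about equally and the loss is much larger. The specified model is a Poisson mixed model with an at-risk offset and random home effects, not an unweighted comparison of home means. With the plan's variance split as 0.08 between and 3.92 within homes, inverse-variance weights after 10% loss are about 2.1 to 1 for a home of 45 against one of 15. Power for equal thirds at 15, 30 and 45 is then 79.1%.

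None of this removes the core point: 1.58 is the equal-size minimum, and the article plans for unequal homes.

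**Conclusion.** The point holds as a conditional one. The stated 80% power for a difference of 0.49 after 10% losses is tied to equal-sized homes, a premise that the article's own recruitment and analysis sections contradict, and the reserve is only 0.7 points. For an assumed CV of 0.4 to 0.6, power is about 76% to 79% with 810 analysed and about 78% to 82% if all 900 contribute fully.

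These figures take the plan's variance of 4 and ICC of 0.02 as given, use the normal approximation that reproduces the plan's numbers, and assume that losses leave the CV unchanged. The effect is modest and does not threaten the design. It does mean that the sample size statement should be corrected.

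**What to change.** In Sample size estimation, replace 1.58 with 1 + ((1 + CV^2) x 30 - 1) x 0.02, or with the mixed-model equivalent (b), and state which is used. Take the CV from the bed numbers of the roughly 65 eligible homes; segmenting homes by size already requires those numbers. Then restate either the power at 900 recruited and 810 analysed, or the difference detectable with 80% power (about 0.51 at CV 0.5 under formula (a)).

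The cost is one recalculation and a reworded paragraph. No extra residents or homes and no change of design are needed. The downside is a slightly less favourable stated power.

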### Intervention

This is the first study that brings together a multi-disciplinary team to review the medications of care home residents in a face-to-face meeting where they are able to draw on, and benefit from, one another's expertise. The intervention is a multi-professional medication review meeting involving a clinical pharmacist and pharmacy technician from the PCT MMT, care home staff and GP(s) responsible for the medical care of residents. All pharmacists (n = 4 to 8) and technicians (n = 4 to 8) participating in this study have previous experience of reviewing the medication of care home residents. It is hypothesised that this model of medication review service has greater potential to deliver benefits to patients than a pharmacist working in isolation on a medication review (i.e. examining patients' clinical records and making recommendations to the GP at a later date in writing or face-to-face).

The first medication review meetings will take place at the care homes approximately four weeks after allocation to treatment and a second medication review will take place at the 6 month point after allocation to treatment. Each medication review meeting will (on average) consider 15 residents and is expected to last for up to two hours. Thus two face-to-face meetings will be necessary for a care home with around 30 residents and more than two will be required for larger care homes.

The medication review meeting is organised by the pharmacy technician from MMT. The technician will liaise with the care home, GP(s) and the clinical pharmacist (MMT) in order to agree a date and time for the meeting(s). As part of the process of consent, GP practices and care homes have agreed to commit staff time to the medication review meetings. The technician is also responsible for the necessary data extraction from GP practices prior to the medication review meeting. This involves generating patient summary data (see below) - information that allows the clinical pharmacist to complete their preparation for the review meeting.

About one month prior to the intervention (or medication review meeting), a PCT MMT pharmacy technician will visit the care home and obtain a list of residents and their associated GP practices, plus ensure relevant blood tests have been requested with district nurses. Two weeks prior to the planned review meeting the technician will obtain a computer-generated patient summary from the GP practices for each resident to be reviewed. This will include details of current medication, past medical history and recent blood tests. The patient summary data is passed to the clinical pharmacist from MMT. As part of their preparation for the medication review meeting, the clinical pharmacist will prepare a pharmaceutical care plan for each care home resident considering a number of factors, including: the indication, need, evidence base and PCT guidelines for each medication and medical problem. The care plan will also consider any interactions, unmet pharmaceutical needs and clinical appropriateness of each medication.

During the review meeting, each resident's care plan and the associated list of recommended actions prepared by the clinical pharmacist will be discussed by the multi-disciplinary team. As the meeting takes place at the care home, the Medicines Administration Record (MAR) Charts can be consulted during the course of the discussion and any discrepancies with the resident care plan will be identified. A joint decision on action plans will be agreed by the clinical pharmacist, GP, care home staff and, where appropriate, the care home resident. The medication review meeting also provides care home staff with the opportunity to discuss with the clinical pharmacist any general issues relating to medicines management at the care home.

After the review meeting, agreed action plans will be implemented by MMT. The pharmacy technician will update GP records and Read Code the medication review. In addition, the technician will provide written details of all agreed medication changes to the care home and dispensing community pharmacist.

For those MMT members who are not as experienced in care home medication reviews, training on study protocols will be provided by senior members of the MMT. Where a clinical pharmacist undertakes a medication review at a care home for the first time, a senior colleague will evaluate the process and provide feedback. Peer support from more experienced colleagues will be available to members of MMT throughout the study.

The medication review is not designed to focus specifically on issues associated with falls, however many of the interventions which are recommended by pharmacists in medication reviews are likely to impact this outcome, as drug related falls are an important cause of morbidity [30]. Examples include: stopping medication which causes confusion (e.g. psychotropic medication) or adjusting medication which improves mobility (e.g. for Parkinson's disease). It is recognised that the falls prevention context is important and that any fall prevention initiatives that are put in place during the study period have the potential to influence the analysis. While it is envisaged that any falls prevention initiatives would be rolled out consistently across treatment and control, members of the Management Group and Trial Steering Committee (see section entitled Support for the study) will advise the research team of any developments pertinent to the conduct of the study.

### Data collection

Data will be collected from intervention and control homes at three points (baseline, 6 months and 12 months) as follows. All patient demographic, medical history, medication details and falls data (in previous six months) will be obtained from records in the care home (i.e. individual care plans and accident books) and GP practices by a pharmacy technician one month prior to the planned care home visit in intervention homes. For the control homes, data collection at baseline will take place as soon as possible after allocation (within a month of allocation) and will be facilitated by the pharmacy technician. The data collected at this point will include patient demographic and falls data.

Details of all recommendations arising from the medication review, as well as implemented interventions, will be recorded for intervention homes. This process will be repeated after six months. After 12 months follow-up this data will again be extracted from care home records and GP practices (for intervention and control homes, with data collection for the latter encompassing the 6 month and 12 month points) by a pharmacy technician. Anonymised data will be passed to the research team for analysis.

For the economic evaluation, data will be collected on the time taken to develop and provide the intervention and on the resource items likely to change as a result of the intervention. Resource items will include visits to (and from) health care professionals (such as GP, nurse and dietician), as well as hospital and social services.

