### Eligibility of care homes

There are more than 130 care homes in the PCT area, but after all exclusions it is predicted there will be approximately 65 care homes eligible for participation.

In order to take part the care homes must be for older people (average age >65 years) and have been registered with the Care Quality Commission (CQC) for at least six months. Care homes specifically for people (of all ages) with learning disability, sensory impairment, mental health problems, physical disabilities and alcohol dependence will be excluded. Care homes will also be excluded if they have received a medication review service from the PCT in the last 6 months, if they receive the services of a community geriatrician or if they are subject to investigation of the safeguarding of vulnerable adults.

As consent is being sought at the care home level, residents who self-medicate will be excluded. Those residents who are in the home for respite care will also be excluded.

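### Residents are listed and baseline data taken at or after allocation, on a different trigger in each arm, when both could be done before minimisation at little cost

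*Protocol article*

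**What the plan says.** All references are to the protocol article.

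- **Allocation to treatment:** "consenting homes will be allocated to intervention or control sequentially after consent is obtained using minimisation".
- **Intervention:** "The first medication review meetings will take place at the care homes approximately four weeks after allocation to treatment". About a month before that review, "a PCT MMT pharmacy technician will visit the care home and obtain a list of residents and their associated GP practices". The same section makes the technician who organises the review responsible for extracting GP data for it, and gives the number of technicians as 4 to 8.
- **Data collection, intervention homes:** demographic, medical history, medication and falls data are obtained "by a pharmacy technician one month prior to the planned care home visit in intervention homes".
- **Data collection, control homes:** "For the control homes, data collection at baseline will take place as soon as possible after allocation (within a month of allocation", facilitated by the pharmacy technician. On content: "The data collected at this point will include patient demographic and falls data". Follow-up is extracted by a pharmacy technician after 12 months, "with data collection for the latter encompassing the 6 month and 12 month points".
- **Eligibility of care homes:** "residents who self-medicate will be excluded", as are respite residents. No date is given for applying either exclusion.
- **Clinical analysis:** falls are aggregated by home as events over resident-days at risk, with home size and resident type as fixed effects. STOPP counts are modelled per patient, with that patient's baseline count as covariate.

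**The concern.** In a cluster trial, randomising homes protects the comparison only if the people counted in each home, and what is recorded about them beforehand, do not depend on the arm. Here both appear to be settled once the arm is known.

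Two things are exposed. The first is cohort membership: who is treated as self-medicating or as a respite stay, and who has arrived or left by the time the list is made. The second is the baseline STOPP count, which enters the model for one of the two primary outcomes as if it had been measured before randomisation. The two arms also start from different events: a planned review visit in one, the allocation itself in the other.

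**Working it through.** **Sequence.** Let A be the day a home is allocated.

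- Home consent: before A (Allocation to treatment).
- Intervention review: about A + 4 weeks (Intervention).
- Intervention list and baseline: about one month before the review (Intervention; Data collection). That is A + 4 weeks − 1 month, or about A. A review can be planned only once a home is known to be an intervention home, so the practical reading is at or just after A.
- Control baseline: between A and A + 1 month (Data collection, explicit).

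The post-allocation baseline is thus stated for control homes and follows from the timings for intervention homes. Baseline dates relative to allocation can differ between arms by up to about a month. If control homes use the same six-month look-back for falls, up to 1/6 (about 17%) of that window could lie after allocation.

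**Who and what.** Listing in intervention homes is by a technician of the Medicines Management Team, which delivers the review and implements its actions. In control homes the article says only the pharmacy technician, which reads as the same role but is not spelled out. The control baseline sentence names demographic and falls data. It says these are included, so it does not rule out medication data, but it does not name the data needed for the STOPP covariate.

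**Which analyses are touched.** The STOPP model uses a measured baseline. The falls model does not: its fixed effects are the intervention, home size and resident type. For falls, the exposure is only through who contributes events and days at risk.

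**Scale.** The article gives no figure for a bias, so none can be derived. A yardstick comes from its own sample size inputs: difference 0.49 falls per patient per six months, variance 4, intra-cluster correlation 0.02, 30 residents per home, 80% power, 5% two-sided.

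- Planned size: 2 × 4 × (1.960 + 0.842)² / 0.49² = 261.5 per group (article: 261).
- Design effect: 1 + 29 × 0.02 = 1.58 (article: 1.58).
- Total: 2 × 261 × 1.58 = 824.8 (article: 824). The plan's figure reproduces.
- Standard error of the difference: √(2 × 4 × 1.58 / 412) = 0.175.

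With no true effect and an assumed between-arm bias b, the two-sided false-positive rate is 1 − Φ(1.96 − b/0.175) + Φ(−1.96 − b/0.175):

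| Assumed b | Share of 0.49 | False-positive rate |
|---|---|---|
| 0.05 | 10% | 5.9% |
| 0.10 | 20% | 8.8% |
| 0.20 | 41% | 20.8% |
| 0.30 | 61% | 40.2% |

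As a concrete case, suppose two of 30 residents, each falling at twice the mean rate of 1, are left off in every home of one arm. The mean becomes (30 − 4)/28 = 0.93. The shift of 0.07 is about 0.4 standard errors (0.07/0.175), and the false-positive rate is roughly 7%.

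**The case against.** The strongest reply concerns selection. Recruitment bias in cluster trials usually enters through individual consent after allocation, and this trial has none. The Recruitment section takes consent at home level and has all residents reviewed. Discretion is left only over self-medication, respite status and turnover. That stands, and it makes selection a limited risk.

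A reader might infer that post-allocation baselines also compromise the falls analysis. The Clinical analysis section does not support this. Baseline falls do not enter that model, and its adjustment factors are characteristics by which homes are segmented before allocation. Baseline falls are also read from existing records of the previous six months, most of which predate allocation, and both arms' baselines precede any review.

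A reader might also infer that the technician who served a home extracts its 12-month outcomes, so that detection bias is built in. The article says only that a pharmacy technician does so, out of 4 to 8. It describes no masked extraction, but an article commonly leaves such procedure to the full protocol, so its silence is no finding.

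What the reply does not remove is the order of events. The control baseline is explicitly after allocation, and the intervention list and baseline fall at about the same point on a different trigger.

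**Conclusion.** The point holds in a limited form. The resident list, and with it apparently the exclusions and the STOPP baseline covariate, is set at or after allocation, with arm-specific timing and, in intervention homes, by the delivering team. This rests on one explicit statement (control baseline), one deduction from stated intervals (intervention list and baseline) and one inference (exclusions are applied when the list is made, since no date is given and no earlier list is described).

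The size of any resulting bias is unknown. The drop from 1.00 to 0.93 might be taken as an estimate of a 7% spurious effect. It is not: it assumes two high-rate residents per 30 omitted in every home of one arm, all in the same direction, and nothing in the article suggests that this will happen. The point is an inexpensive improvement to make, not a defect that undermines the trial.

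**What to change.** Change the order. After home consent and before minimisation, make a dated list of eligible residents with the self-medication and respite exclusions applied. Extract baseline falls and the medication data needed for STOPP at that time, on the same schedule in all homes. Then allocate. Allocation stays sequential, which is the practical advantage the Allocation to treatment section wants.

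Use the list to define the baseline cohort for the STOPP analysis. Keep events and days at risk for falls as planned, with the same listing rules in both arms. The list should not turn the falls analysis into a closed cohort.

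As a secondary step, where rostering among the existing 4 to 8 technicians allows, have follow-up extracted by one who did not serve that home, and score STOPP from medication data with the arm removed. This reduces unmasking but cannot guarantee masking, because reviews are Read-coded in the GP records.

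Cost: each home's allocation waits for one extraction. The present listing visit also serves review preparation, such as checking that blood tests have been requested, so intervention homes may need one further contact after allocation.
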